## Abstract

**Background:**

Fractures associated with bone fragility in older adults signal the potential for secondary fracture. Fragility fractures often precipitate further decline in health and loss of mobility, with high associated costs for patients, families, society and the healthcare system. Promptly initiating a coordinated, comprehensive pharmacological bone health and falls prevention program post-fracture may improve osteoporosis treatment compliance; and reduce rates of falls and secondary fractures, and associated morbidity, mortality and costs.

**Methods/design:**

This pragmatic, controlled trial at 11 hospital sites in eight regions in Quebec, Canada, will recruit community-dwelling patients over age 50 who have sustained a fragility fracture to an intervention coordinated program or to standard care, according to the site. Site study coordinators will identify and recruit 1,596 participants for each study arm. Coordinators at intervention sites will facilitate continuity of care for bone health, and arrange fall prevention programs including physical exercise. The intervention teams include medical bone specialists, primary care physicians, pharmacists, nurses, rehabilitation clinicians, and community program organizers.

The primary outcome of this study is the incidence of secondary fragility fractures within an 18-month follow-up period. Secondary outcomes include initiation and compliance with bone health medication; time to first fall and number of clinically significant falls; fall-related hospitalization and mortality; physical activity; quality of life; fragility fracture-related costs; admission to a long term care facility; participants’ perceptions of care integration, expectations and satisfaction with the program; and participants’ compliance with the fall prevention program. Finally, professionals at intervention sites will participate in focus groups to identify barriers and facilitating factors for the integrated fragility fracture prevention program.

This integrated program will facilitate knowledge translation and dissemination via the following: involvement of various collaborators during the development and set-up of the integrated program; distribution of pamphlets about osteoporosis and fall prevention strategies to primary care physicians in the intervention group and patients in the control group; participation in evaluation activities; and eventual dissemination of study results.

**Study/trial registration:**

Clinical Trial.Gov NCT01745068

## Background

Among Canadians over 50 years of age, close to two in five women and one in six men will experience at least one fracture due to bone fragility (FF) [1-3], in other words a fracture resulting from minimal trauma or a fall that would not harm a healthy person. In women over age 50, the annual FF incidence rate is 14/1000, twice the incidence rate of cerebrovascular incidents and myocardial infarcts combined [4]. FFs cost Canada’s healthcare services over $2 billion annually [5,6], with costs expected to triple over the next 20 years [7,8].

Recent statistics reveal that about two million Canadians suffered from osteoporosis defined by bone mineral density (BMD) [9], but BMD is an imperfect measure of bone strength. Although FFs are generally related to bone fragility related to osteoporosis [1,10-13], and the relative risk for FF increases with decreasing BMD, the majority of FFs occur in individuals without BMD-defined osteoporosis. The occurrence of a FF is a sentinel event predicting a future FF [14], at least doubling the risk of secondary fractures compared with age- and BMD-matched individuals without a FF [15,16]. Indeed, men and women with a hip or spine FF are at high risk for repeat fractures, irrespective of their BMD results, which may be normal. Of note, about half of hip fracture patients have sustained previous FFs [17,18], suggesting that FFs are events that should guide preventive interventions. Hip fractures often precipitate decline in health or even death, and loss of mobility, with high associated costs for patients, families, society and the healthcare system [19-23].

The two mainstays of FF prevention are pharmaceutical interventions to strengthen bones, and fall prevention programs to maintain and improve strength and balance, including other strategies to reduce fall risk factors, keeping in mind that exercise also strengthens bones. The success of interventions to manage FFs more effectively, to identify and treat those with bone fragility, to maximize population health by preventing or delaying frailty, and to minimize costs [24-28] is mediated by the context of interventions within the local healthcare system [29,30]. Despite strong evidence of their effectiveness, prescription and adherence to osteoporosis treatment and fall prevention interventions following FFs remain sporadic and inconsistent in primary care. It is hoped that when post-fracture screening and fall prevention programs are systematically integrated, and secondary FFs may be prevented in an additive or even synergistic manner [30,31].

In the context of current primary care reform, secondary fracture prevention program research must evaluate multidisciplinary and interorganizational strategies, with attention to the regional context of implementation, the providers, and the participants. The present paper includes the design and evaluation procedures for a novel secondary FF prevention program, involving collaboration between secondary healthcare practitioners (orthopedic surgeons and medical bone specialists), primary care physicians (PCPs), group practice nurses, and local and provincial fall prevention programs, being implemented in the province of Quebec, Canada. This work builds on the Osteoporosis and Peripheral fractures: Treatment and Investigation through Multidisciplinary care at the CHUS (OPTIMUS) intervention. The proposed intervention involves PCPs in the evaluation and treatment of osteoporosis following FFs treated by orthopedic surgeons [32-38] and integrates local and provincial fall prevention programs implemented in the province of Quebec, including the Personalized Multifactorial Intervention (PMI), an individualized program offered to the most frail elders considered at risk for falls [39]; and a community-based fall prevention program aimed primarily at improving balance and strength through exercise for elders who have fallen or are concerned with falls (*Stand Up!*) [40]. This integrated program will be orchestrated by site study coordinators.

The overarching aim is to investigate the effectiveness, cost-effectiveness and cost-utility of an integrated FF prevention program, and to obtain a portrait of the barriers and facilitating factors for such programs. More specifically, the objectives are:

1. to combine existing fall prevention and post-fracture management programs in the province of Quebec into integrated interdisciplinary FF prevention programs;

2. to compare the performance of these integrated programs to results from control sites, using a pragmatic study design;

3. to identify barriers as well as factors that improve effectiveness across different implementation regions;

4. and to develop and engage in active knowledge transfer activities in Quebec regions where integrated FF prevention programs are neither adequately nor successfully implemented.

### Research questions and hypotheses

#### Primary question

Can an integrated FF program reduce the risk of a secondary FF in a population of patients 50 years of age and over, who sustained a FF 18 to 20 months previously?

#### Secondary questions

1) Can a post-FF management program be successfully integrated with PCPs’ health care, and local and national fall prevention programs, from a patient and healthcare system perspective?

2) Is this integrated FF prevention program effective and cost-effective?

3) What are the barriers and factors that improve effectiveness across different implementation regions?

Drawing upon the literature on integrated healthcare, fall and fracture prevention, as well as the OPTIMUS study [32-38], we hypothesize that an integrated FF program can reduce the risk of a secondary fracture by at least 30% in the population of interest. In addition, by examining the implementation process of the program, we will make recommendations to circumvent the barriers to implementation, and to build upon the factors that lead to improved integration of the care providers involved in the program.

#### Conceptual framework

The research program will draw on the key principles of the Development Model for Integrated Care (DMIC) [41-43] to implement the proposed intervention, and the Model of Structuration of Interprofessional Collaboration (MSIC) to explore interorganizational collaboration and its links to the selected clinical outcomes [44].

The DMIC is a recent model for the development of an integrated program [41-43] that has been validated through a panel of Dutch experts and is currently implemented within three settings in The Netherlands. This project will tap into the first and second phases of the DMIC model: Initiative and design; and Experiment and execution. These serve as a checklist for the development of the program in each intervention region, and as a guideline during the focus group discussions with the participating healthcare professionals involved in the intervention.

The MSIC lists 10 indicators, grouped into four dimensions: Shared goals and vision; Internalization; Formalization; and Governance. These indicators capture facets of relationships between individuals engaged in a collaborative practice, and the organizational context in which they work [44]. The MSIC has been validated in various healthcare contexts, mostly in the province of Quebec [45-47]. It will be used to guide the evaluation of collaboration among practitioners and organizations involved in the program (hospitals, orthopedists and medical bone specialists, PCPs in private practices, family medicine group (GMFs), and provincial and local fall prevention services).

## Methods

### Study design

A pragmatic, controlled trial design is being used to assess whether the intervention works in a setting that is as similar to routine practice as possible [48]. Within such a design, all participants are enrolled unless the study intervention might compromise patient safety; treating physicians and healthcare practitioners decide how the intervention is delivered; integrated models of healthcare are encouraged, as the intervention is delivered through the participation of a spectrum of practitioners in a range of healthcare organizations; and an intent-to-treat analysis is the only analysis possible [48-52].

### Ethical approval

Given the large number of organizations involved, ethical aspects of this study were evaluated via a multi-center mechanism as recommended by the Ministère de la Santé et des Services Sociaux (MSSS). The Comité d’éthique de la recherche en santé chez l’humain du Centre hospitalier universitaire de Sherbrooke (CHUS) served as the principal ethics board and approved the final documents.

### Participants

The study population consists of community-dwelling males and females, who are 50 years of age and over, who have a PCP (this is the case for 94% of this age group in Canada [54]), who are able to follow simple instructions, and who have sustained a FF within two months of the recruitment date. Participants presenting with the following conditions will be excluded: fracture at sites not commonly associated with osteoporosis such as toe, finger, hand, foot, patella, head, and cervical spine; severe kidney insufficiency (grade 4 or 5); or an advanced stage of cancer or any other disease from which the patient is likely to die within the next year.

### Recruitment

Drawing upon the methodology of previous studies in a similar population [32-34,55], participants for intervention sites will be recruited by a study coordinator over a period of 12 months, and will provide their informed consent to participate and complete the baseline questionnaire. Three methods will be used to recruit intervention group participants:

1. Patients with FFs in participating outpatient orthopedic clinics will be identified by a study coordinator;

2. Hip fracture inpatients will be approached on the ward during their hospitalization;

3. And hospital emergency and ward discharge administrative data will be scanned for patients with a primary discharge code typical of a FF. These participants will be contacted by mail by the hospital to inform them about the research project and that a local study coordinator will contact them. Electronic discharge data allows patient identification within one week following discharge.

Due to budgetary and ethical considerations, only strategy 3 will be used to recruit participants in the control hospitals/regions. Should it be required as an alternative, FF patients’ identification through the *Régie de l’assurance maladie du Québec* (RAMQ) database will be considered, as in the Recognizing Osteoporosis and its Consequences in Quebec (ROCQ) study [55]. The main limitations of this alternative strategy as well as strategy 3 are a delay required to obtain patients’ information (estimated at two months in the case of the RAMQ data, one week for the hospital administrative data), and a potential selection bias (those more at risk for fractures, or who are younger and more educated may be more likely to consent); however, such strategies might be an efficient way to increase the external validity of the study by recruiting a broader range of fracture patients.

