### Outcomes and data collection

All participants will be followed for a period of 18 months. A multilevel approach is being used, in which outcomes at the patient level will be measured with quantitative tools, and outcomes at the organization level (*e.g*., perception of the degree of integration and collaboration between organizations) will be measured simultaneously using qualitative techniques [57]. Combining both qualitative and quantitative measures will allow a better understanding and contextualisation of the quantitative results, and verification as to how organization level factors impact the effectiveness outcomes [57,58].

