### Statistical analysis

#### Sample size

##### Quantitative evaluation of entire cohort

Based on preliminary (almost four years follow-up) results from the OPTIMUS project, the incidence of a secondary fracture at 16 months in the control group is expected to be 10%; therefore, this incidence of fracture was used as a proxy for the sample size calculation of this project (primary outcome measured at 18 months). Considering the reported efficacy of antiresorptive drugs among others (average absolute reduction rate of 4%) [74-77], the results obtained in the intervention group of the OPTIMUS cohort (expected absolute reduction rate in FF of 2.5%), as well as the expected synergy with fall prevention programs, and collective orders that will allow for a rapid pharmacological intervention, an absolute reduction of 3% (*i.e*., a secondary fracture incidence at 18 months of 7% in the intervention group) is a conservative estimate of the effect to be detected. Under these assumptions and assuming a power of 80% and an alpha level of 5%, 1,356 participants per group are necessary to verify the primary hypothesis. It is estimated that approximately 15% of the participants will be lost to follow-up or will withdraw from the study prior to the 18-month data collection time point. Therefore, a total of 1,596 participants will be recruited in each group (total N = 3,192).

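### The RAMQ fallback is estimated to take two months to supply patient information, which uses up the whole two-month eligibility window

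*Protocol article*

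**What the plan says.** The protocol article sets the eligibility window under Participants: people "who have sustained a FF within two months of the recruitment date". The primary question agrees with this. It concerns patients "who sustained a FF 18 to 20 months previously", which is entry at 0 to 2 months plus the follow-up given under Outcomes and data collection ("All participants will be followed for a period of 18 months").

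Under Recruitment, intervention sites find patients in orthopaedic clinics, on the ward and through hospital administrative data. For controls, "only strategy 3 will be used to recruit participants in the control hospitals/regions", that is, the hospital administrative data. After identification there are two further steps, a letter and then an approach by the coordinator: "These participants will be contacted by mail by the hospital to inform them about the research project and that a local study coordinator will contact". No duration is given for either step.

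The fallback comes directly after the sentence on controls and is conditional: "Should it be required as an alternative, FF patients’ identification through the" RAMQ database is to be considered. The same paragraph lists the delay in obtaining patient information as a limitation, "estimated at two months in the case of the RAMQ data, one week for the hospital administrative data". It does not compare that delay with the eligibility window.

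**The concern.** A backup route should be able to deliver eligible patients if the main route falls short. This one is expected to deliver names at about the moment the patients stop being eligible, with a mailing, a call and consent still to come. There are two possible consequences:

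- **Window enforced.** The fallback adds few participants, and a recruitment shortfall stays a shortfall.
- **Window not enforced.** Patients enter more than two months after fracture and finish follow-up after month 20, outside the primary question. The fallback's place in the text suggests that it mainly serves controls, although the wording names no arm. The 18-month clock would then start later after fracture in one arm than in the other.

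**Working it through.** **1. The plan's own sample size.** Inputs from Sample size: 10% v 7%, 80% power, alpha 5% (taken as two-sided), 15% loss.

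n = [1.960·√(2·0.085·0.915) + 0.842·√(0.10·0.90 + 0.07·0.93)]² / 0.03² = (0.773 + 0.331)² / 0.0009, which gives 1,356 per group. Then 1,356 / 0.85 = 1,595.3, so 1,596. Both stated figures reproduce and are not in dispute.

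**2. Time left for contact and consent.** Two months is 2 × 30.44 = 61 days.

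- RAMQ: 2 − 2 = 0 months.
- Hospital data: 61 − 7 = 54 days, counted from discharge.

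The article does not say when the RAMQ delay starts. If it starts at discharge or claim rather than at fracture, the conflict is tighter.

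**3. Share of RAMQ-identified patients still eligible.** Assume that the delay is normal with mean 61 days and SD s, and that mailing, call and consent take L days. Then P(delay + L ≤ 61) = Φ(−L/s). The article gives neither s nor L, so a range is shown.

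| Contact time L | s = 3 days | s = 7 days | s = 14 days |
|---|---|---|---|
| 7 days | 1% | 16% | 31% |
| 14 days | 0% | 2% | 16% |
| 21 days | 0% | 0.1% | 7% |

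A still wider spread (s = 21) gives 37%, 25% and 16%.

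**4. If the window is enforced.** Suppose a share f of the 1,356 evaluable controls had to come from RAMQ and none qualified, with the intervention arm complete. Both values of f are assumptions.

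- f = 25%: 1,356 × 0.75 = 1,017 controls, power about 74%.
- f = 50%: 1,356 × 0.50 = 678 controls, power about 64.5%.

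**5. If late patients are enrolled, in the control arm only.** Assume 10% incidence over months 0 to 18 after fracture, with the hazard in the first two months m times the later hazard h. Then h = −ln(0.9)/(2m + 16), and incidence over months 2 to 20 is 1 − exp(−18h).

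| m | Incidence, months 2 to 20 | Change from 10% |
|---|---|---|
| 1 (constant) | 10.0% | 0 |
| 1.5 | 9.5% | −0.5 points |
| 2 | 9.05% | −0.95 points |
| 3 | 8.26% | −1.74 points |

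These changes are for every control entering at month 2 against entry at fracture. They scale with RAMQ use: with m = 2 and a quarter of controls affected, 0.25 × 0.95 = 0.24 points. The values of m are assumptions. The table shows direction and sensitivity and does not estimate the bias in this trial.

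**The case against.** The strongest reply is that this concerns a contingency. The planned control route identifies patients within a week of discharge and leaves about 54 days. The RAMQ route is only to be considered, and only if needed. That stands: unless the fallback is used, the planned comparison is untouched by this conflict.

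A reader might infer more, namely that the arms will differ systematically in time since fracture and that early re-fractures in controls will go unseen. The article does not support this. As written, the eligibility rule excludes late patients, so the direct consequence is low yield. A shifted time origin needs a breach of the window, mainly for controls, which the article nowhere describes.

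A reader might also want a fixed size for the bias. The article gives no hazard over time since fracture and no expected share of RAMQ patients. Comparing very early entry with entry at two months sets two eligible times against each other, and intervention sites use the hospital-data route too. Nor would this mechanism produce a false benefit: under a falling hazard, later control entry lowers control risk and dilutes the effect.

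Finally, the article names the delay as a limitation, expects route-related selection bias (Discussion), and promises adjustment for baseline differences (Data analysis). This is a partial answer. The general commitment could cover time since fracture, but the delay is never set against the window. The selection bias under Discussion points to higher risk in controls, whereas late entry could lower it. Two stated figures that collide are not a detail left to an analysis plan.

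**Conclusion.** The conflict is real and follows from the article's own figures: a two-month delay leaves zero days of a two-month window. How few patients would remain eligible depends on assumptions, about 0 to 31% for SDs of 3 to 14 days and contact times of 7 to 21 days. It would therefore be too strong to say that the route yields almost nobody. The consequence is conditional on using RAMQ. It is lost recruitment if the window is kept. If the window is breached for controls only, it is a possible dilution of the effect, whose size the article does not determine and which is zero under constant hazard. This is a correction to make before the fallback is used; it is not a fault in the planned primary comparison.

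**What to change.** Reconcile Primary question, Participants and Recruitment before any use of RAMQ, in one of two ways:

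- remove the fallback; or
- state one eligibility window that applies identically to both arms and to every recruitment route, and restate the 18 to 20 months of the primary question if the window changes.

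In either case, record days from index fracture to enrolment for every participant, and include that interval as a covariate in the logistic model already planned for the primary outcome. Recruitment routes differ by arm even without RAMQ, so the interval may differ too. The fracture date is already needed to check eligibility.

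The cost is a short amendment and one extra covariate, plus either the loss of a fallback of little use or the admission of some later patients. An analysis on time since fracture with delayed entry at enrolment is an option and not a requirement; the planned 18-month comparison can stay.

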### Study interventions

#### Intervention group

Nurses working in the Family Medicine Groups and Cliniques-Réseau (in Montreal) (GMF/CRs) located in the areas served by the recruiting hospitals will receive a workshop on evidence-based pharmacological interventions for osteoporosis, and benefits of exercise and fall prevention strategies to prevent FF. All PCPs within the intervention group regions will receive a pamphlet summarizing the workshop.

Upon recruitment, FF participants will be educated by the study coordinator about osteoporosis as the cause of their FF, the importance of a rapid screening evaluation for potentially treatable primary causes of bone fragility, the benefits of early and prolonged treatment, the options for treatment to be adapted for individuals, and will be asked permission to contact their PCP and community pharmacist. Participants’ PCPs will receive written information containing a presumed osteoporosis diagnosis, investigations to be performed, correct interpretation of bone densitometry results in the context of a FF, treatment options adapted to the individual patient, and alternatives if the first prescriptions are not tolerated or are stopped.

The integrated intervention *per se* includes the following:

1. When possible, screening basic blood tests (*e.g*., calcium, phosphate, white blood cells, hemoglobin, platelets, vitamin D) in the context of a FF will be performed at the recruiting hospital laboratory, and the results will be transmitted to the participant’s PCP with a personal letter explaining the importance of seeing the patient rapidly (ideally within one month), and the urgency of initiating an osteoporosis treatment. If the PCP is part of a GMF/CR [56], then the clinic nurse will receive a copy of the information sent to the PCP.

2. Following a region-specific *a priori* defined algorithm to identify the most relevant resource for the participant, the study coordinator or the GMF/CR nurse (when possible) will orient the participant to an appropriate fall prevention program, and organize his/her registration or placement on the waiting list. A local exercise and fall prevention program appropriate for the patient according to the participant’s age, fracture risk, and abilities will be agreed upon by the study coordinator and the participant. The study coordinator will work with numerous local fall prevention champions supporting this research program, to establish and maintain an up-to-date list of available exercise and fall prevention programs at each site. The study coordinator will also encourage the participant to engage in additional physical activities at a comfortable level of intensity.

3. The participant will be called quarterly by the study coordinator or the GMF/CR nurse to monitor pharmacological treatment adherence, to detect and correct (if appropriate) inadequate intake or side effects affecting compliance, to answer questions, to encourage compliance, and to track fall and fracture information recorded in the participant diary.

4. The study coordinator or the GMF/CR nurse will communicate with the participant’s pharmacist at 6 and 12 months to confirm drug delivery to the participant (if the participant has been prescribed osteoporosis pharmacological treatment), and if possible to enlist this professional’s help in encouraging treatment.

5. At each follow-up, if the patient is not taking an adequate pharmacological treatment, a letter will be sent again to the PCP (and the GMF/CR nurse, if appropriate) suggesting that they treat the patient according to the participant’s 10-year fracture risk.

6. Participant adherence to the fall prevention program will be monitored at the mid-point and at the end of the program. If necessary, the study coordinator will arrange a program change to better fit the participant’s needs.

